#### Baseline variables and other outcomes

Anthropometrics

Body weight (in kilogrammes) and body height (in centimetres) will be collected and presented as mean and SD. Time-point: Baseline (*t*_0_).

Education level

A study-specific questionnaire will be used to collect data on education level (five levels ranging from compulsory school to university degree). Time-point: baseline (*t*_0_).

Comorbidities

Charlson Comorbidity Index [47] will be used to quantify the burden of comorbid conditions. The occurrence of any of 19 different comorbid conditions is assigned a weight (ranging between 1 and 6), and the resulting metric is the sum of weights. Higher weights indicate a higher risk of mortality and more severe comorbidity. Results are presented as medians and proportions. Time-point: baseline (*t*_0_).

Current medications

Medical journals and interviews will be used to collect data on current medications. Time-point: baseline (*t*_0_).

Smoking and alcohol habits

A study-specific questionnaire will be used to collect information on smoking habits and alcohol use. Smoking will be assessed by interview and classified into three levels: *current smoker*, *previous smoker*, and *never smoker*. Alcohol habits will be assessed by the question “How many glasses of alcoholic beverages do you consume every week?” and answers are categorised into five levels (none to >14/week). Time-point: baseline (*t*_0_).

Nutritional status and risk of malnutrition

Collected by interview, three areas will be used to assess nutritional status: *current underweight* (BMI<20 for patients under the age of 70, BMI <22 in patients over the age of 70), the occurrence of *unintentional weight loss* (yes or no), *perceived difficulties eating* (yes or no) [48]. If any of these three areas are fulfilled (low BMI or answered yes), the risk of malnutrition is considered heightened. Time-point: baseline (*t*_0_).

Cognitive impairment

The Swedish version of the Mini-Mental Test Examination (MMSE-SR) [49] assesses cognitive impairment. Higher scores indicate better cognitive status (maximum 30 points). A cut-off of <24 points is indicative of cognitive impairment. Time-point: baseline (*t*_0_).

Patient-centred goals of exercises

The PSFS-scale [33] is used in the intervention group to capture a minimum of one and a maximum of three situations/activities that they perceive as important in their lives but challenging to perform due to their medical condition. PTs design exercise regimens to improve chosen activities. The outcome is the specific activity (1 to 3) and grading of how difficult it is to perform (1 to 10). Time points: (*t*_0_ to *t*_1_).

### Participant timeline {13}

The participant timeline is shown in Table 1.

### Sample size {14}

The sample size was calculated based on the primary hypothesis that the intervention would (1) result in better physical performance measured by the 6MWT pre-surgery and (2) result in 1 grade lower post-operative complications according to CD classification 30 days post-surgery. The standard deviation (SD) used in the sample size calculations were based on data reported in a previous study [10]. For both outcomes, the calculations are based on the assumptions of equal group size and calculated for the independent t-test.

#### Power calculation for 6MWT

For the 6MWT, an SD of 111.5 m was assumed based on a previous study. A clinically important difference of 50 m was used in the calculations. To be able to detect a difference of 50 m, with an alpha level of 5% and a power of 0.80, a total sample size of 160 participants would be needed.

#### Power calculation for CD-classification

For the outcome of post-operative complications, an SD of 1.32 was assumed for the CD scale. A “pitman efficiency factor” was applied by dividing the estimated sample size by 0.864 to adjust for the CD classification as an ordinal scale. We assumed a difference of 1 grade between groups to be of clinical importance. With an alpha level of 5% and a power of 0.80, a total sample size of 58 would be needed. With the application of the correction factor (dividing the total sample size by 0.864), the final sample size needed is 67 evaluable participants.

### Recruitment {15}

Prior to this RCT, a feasibility study was performed [41]. The recruitment rate in the feasibility study was low (35% of eligible participants were recruited). A common reason for declining participation was the need for an extra visit to the hospital for the baseline visit (28%). To counteract this, we now offer taxi transportation to and from pre-operative visits (*t*_−1_ and *t*_1_). Another reason for declining participation was not wanting to delay the time to surgery (14%). The present study places more emphasis on the patient’s clinician informing the participant that no increase in risk is expected in the case of needing to postpone the surgery date for 1–2 weeks to allow for the intervention. More recruitment sites are used in the present study (4 vs 1) than in the feasibility study to lower the total time needed for completion of enrolment.

## Assignment of interventions: allocation

### Sequence generation {16a}

Computer-generated random number tables were constructed using free software, available online (http://www.jerrydallal.com/random/random_block_size.htm) and used for group allocation. Block randomisation with varying block sizes (*n*= 2, 4, or 6) with random ordering is applied to minimise the possibility of predicting group allocation.

### Concealment mechanism {16b}

The allocation table will be uploaded into an electronic database (REDCap), and randomisation will be performed using the randomising function of the database. Full access to the allocation table in the database is restricted to ER and MA, whereas for all other persons involved in the study, the allocation sequence will be concealed.

### Implementation {16c}

MA generated the random allocation table using free software available online (http://www.jerrydallal.com/random/random_block_size.htm). Enrolment of participants is conducted by site-personal (nurses or PTs) whom first approach potential participants identified from a list of patients referred to the hospital for diagnosis and possible surgical treatment. If potential participants match the inclusion criteria, informed consent is obtained by study personnel (nurses or PTs) prior to baseline testing. After the first baseline visit (*t*_0_), participants are randomised and allocated using the randomisation function of the electronic database of the study that ensures the concealment of the allocation order. Randomisation is performed by ER, MA, JD, or ST).

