#### Trial management group (TMG)

The TMG (ER, MA, JD, ST) coordinates all day-to-day operations regarding the study. All participating staff has direct access to the TMG through phone or digital communications for guidance on operational questions. The TMG organises meetings with participating centres (both hospital sites responsible for recruiting participants as well as the primary health care centres) one to two times every semester.

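### Both holders of the allocation table are also among the four who randomise, so allocation is not concealed from the person assigning when either of them does it

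*Protocol article*

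**What the plan says.** Three sections of the protocol article bear on this.

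- Concealment mechanism {16b}: the table is prepared in advance and loaded into the trial database. "Full access to the allocation table in the database is restricted to" two people, both members of the trial management group, "whereas for all other persons involved in the study, the allocation sequence will be concealed".
- Implementation {16c}: one of those two generated the table. Site nurses or physiotherapists enrol, and consent is taken before baseline testing. After the baseline visit, "participants are randomised and allocated using the randomisation function of the electronic database of the study that ensures the concealment of the allocation order". The section then lists four people who perform randomisation, and both table holders are on that list.
- Trial management group (TMG): the group consists of the same four people. It "coordinates all day-to-day operations regarding the study", and all participating staff can contact it directly for operational guidance.

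No section describes a safeguard for randomisations done by a table holder, such as a fixed order in which waiting participants must be randomised, or suspended viewing rights.

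**The concern.** Concealment means that nobody who can affect whether, when or in what order a participant is randomised knows the next allocation. Section {16b} exempts two people from it. Section {16c} then gives those two the task of assigning and still says, without qualification, that the database function secures concealment. A database function cannot hide a list from someone with full access to it, or from the person who made it.

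Selection bias that enters at allocation cannot be reliably removed in the analysis. Participants and care providers are unblinded here (section {17a}), so concealment is one of the few protections available. A report that repeated the sentence in {16c} as it stands would claim more than the described procedure delivers, and a risk-of-bias assessor could read the overlap straight from the article.

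**Working it through.** The plan gives no figure to reproduce. The check sets the role statements side by side and then asks what room they leave.

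**1. Who does what** (sections {16b}, {16c} and TMG)

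| Task | Two table holders | Other two TMG members | Site nurses and physiotherapists |
|---|---|---|---|
| Generated the table | one of them | no | no |
| Full access to the table | yes | no | no |
| Perform randomisation | yes | yes | no |
| Enrol and take consent | not described | not described | yes |

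Only the first column combines access with assigning. The last column keeps enrolment and consent with people from whom the sequence is concealed.

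**2. What access adds.** If full access means that the list can be viewed (assumption), a table holder can know the next allocation every time. For comparison, take someone without the table who sees all past allocations. Assume one central list and block sizes 2, 4 and 6 (section {16a}) equally likely. The best guess is always the arm that is behind. In a block of size 2m the expected number of correct guesses is m + (4^m / C(2m, m) − 1) / 2:

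- size 2: 1 + (4/2 − 1)/2 = 1.50
- size 4: 2 + (16/6 − 1)/2 = 2.83
- size 6: 3 + (64/20 − 1)/2 = 4.10

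The overall rate is (1.50 + 2.83 + 4.10) / (2 + 4 + 6) = 8.43/12 ≈ 0.70. A simulation of 5,000 lists of 160 gives 0.702. Under these assumptions table access raises predictability from about 70% to 100%. The varied block sizes, which {16a} adopts to limit prediction, do nothing against a table holder.

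**3. Room to act on that knowledge.** Eligibility, consent and baseline testing are complete before randomisation, so a table holder who randomises cannot use the list at that step to decide who enters. To change who receives which slot, at least two participants must be waiting together, or one must be held back. Trial status gives March 2021 to about June 2023, roughly 27 months: 160/27 ≈ 5.9 participants a month, or 5.9 × 12/52 ≈ 1.4 a week over all four sites. Holding someone back also uses up the 14–17 days of exercise planned before surgery (section {11a}).

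**4. How many allocations.** If table holders perform a share p of the randomisations, the number is 160 × p. The article gives no p, so the range is 0 (p = 0) to 160 (p = 1).

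**The case against.** The strongest reply is that concealment chiefly protects the decision to enrol, and that this protection is described. Nurses or physiotherapists at the sites enrol and take consent, these steps precede randomisation, and the sequence is hidden from those staff. Section {16b} also names the exception openly, so the sentence in {16c} may be no more than loose wording. Reordering needs two people waiting at once at a rate of about 1.4 a week, and delay is limited by the surgery date.

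Most of this stands. A reader might infer that concealment does not exist at all for randomisations done by a table holder. The documents do not support that: concealment from the recruiting staff is described whoever presses the button, and no section says that a table holder screens, approaches or consents participants. A reader might also infer that about half of the allocations, 160 × 2/4 = 80, are affected. That assumes the four share the work equally, which nothing in the article supports, and it would count allocations made by someone able to see the list, not allocations that were altered. Nothing suggests misuse.

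The reply does not remove the overlap itself. Disclosing the exception in {16b} does not make the unqualified assurance in {16c} true, and a narrow route is still open. The table holders are not remote custodians either: Data Availability identifies one as the principal investigator, and both trained the study personnel (section {18a}). Inclusion involves judgement, for example whether postponing surgery is a medical risk (section {10}), and staff may turn to the management group for operational guidance. Nor is this a detail left to a fuller document, since the article itself states both the access rights and the randomisers.

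**Conclusion.** The point holds in a limited form. Whenever one of the two table holders randomises, the allocation is not concealed from the person assigning, and the assurance in {16c} does not hold for that randomisation. The remaining risk is confined to the order or timing of randomising waiting participants and to influence on site staff through the management group. Its effect on the results cannot be sized from the article, and the number of randomisations concerned is unknown within 0 to 160. The conclusion assumes that full access includes viewing the sequence and that no undescribed safeguard applies. This is a weakness in the separation of duties that should be corrected because correction is cheap. It is not a ground for treating the allocation as unconcealed throughout.

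**What to change.** 1. Let only the two management group members without table access perform randomisation, and delete the two table holders from the list of randomisers in {16c}.
2. Limit the concealment sentence in {16c} to persons without access to the table, so that it agrees with {16b}.
3. In the trial report, state how many participants a table holder randomised before the change. Recruitment started in March 2021, so some may already have been. Section {19} describes audit trails in the database, which should allow the count.

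The cost is a change of user rights and a few edited sentences. The downside is that two people instead of four must cover randomisation. If recruitment is already complete, only the wording and the count remain to be done.

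The change closes the order and timing route for the table holders. It does not remove their contact with site staff, because they stay in the management group. Moving the table to an outside custodian would be an optional extra: it cannot undo what the person who generated the list may know, and separating the two roles does not depend on it.

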## Assignment of interventions: blinding

### Who will be blinded {17a}

Outcome assessors are blinded. Due to the nature of the intervention (exercise), neither care providers nor participants could be blinded. Participants are instructed not to reveal their assignment to assessors at the follow-ups (*t*_−1_, *t*_2_, *t*_3_).

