## Methods: participants, interventions, and outcomes

### Study setting {9}

Screening and recruitment of participants are performed at four sites: Karolinska University Hospital in Solna and Huddinge, South General Hospital, and Ersta Hospital, situated in the Stockholm city area, Sweden.

Physiotherapists (PT) from the Stockholm County home-rehabilitation units will deliver the intervention in the participants’ homes. Fifteen home-rehabilitation units have been recruited to participate in the study, chosen for maximal coverage based on geographical dispersion and for operational purposes limited to the Stockholm County area.

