#### Intervention description {11a}

The intervention group will receive moderate- to high-intensity physical exercise for 14–17 days before surgery. The intervention takes place in the home setting of study participants and is monitored by a PT. A minimum of six PT visits will be performed, and between PT visits, participants are instructed to perform daily unsupervised exercises (tailored to individually chosen goals.

Each daily exercise consists of three blocks of exercises targeting respiratory muscles (block I), aerobic exercises (block II), and functional strength exercises (block III). The target intensity for all exercise blocks is set at 5–7 on the Borg CR-10 scale [31]. Exercises are tailored to the specific goals of participants using the Patient-Specific Functional Scale (PSFS) [32, 33].

*Block I: Inspiratory muscle training* (IMT) performed twice daily for 30 breaths against external resistance. The Powerbreathe K3 device (POWERbreathe International Limited, [name]) is used in the IMT training. The device allows for loading of the inspiratory muscles in increments of 1 cmH2O pressure (minimal load 5, maximal load 200 cmH2O). The initial load is set at 50% av the maximal inspiratory pressure generated at the baseline visit. Participants and PTs are instructed to increase the training load if participants’ rating of exercise intensity at the end of the training session is below 5 on the Borg CR-10 scale.

*Block II: Aerobic exercises* is performed for a duration of 20 min. Exercises are chosen freely by the PT with the possibility to utilise both indoor as well as outdoor activities depending on the living condition of the participants. Exercises utilising an interval training set-up are recommended to allow for periods of high-intensity exercises interspersed with periods of lower intensity.

*Block III: Functional strength training*: A few exercises (“Step-up” and “Sit-to-stand”) are considered essential exercises and are included in the exercise regimen of all participants. These essential exercises are chosen based on the possibility to standardise the increase of training intensity using provided weight belts. Besides these exercises, PTs are instructed to use their discretion in designing exercises to improve patients’ performance on the PSFS-identified activities.

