#### Primary outcomes

Pre-operative outcome: change in maximal walking distance

Difference between treatment groups regarding the change in walking distance during a 6-min walk test (6MWT) [34] during the pre-operative period. The outcome is the maximal walking distance (metres) participants can cover in 6 min. Comparisons between changes in distance between the intervention and control groups will be performed. A difference of 50 m will be considered clinically significant and was used in the power calculations for sample size.

Time points: Baseline (*t*_0_), at hospital admission (or the day before (*t*_1_), and at discharge from hospital (*t*_3_).

Post-operative outcome: complications 30 days post-surgery

The difference in complications between groups regarding post-operative complications (PC) 30 days post-surgery according to Clavien-Dindo (CD) and any complications up to day 30 will be considered [35]. The CD grading system allows for quantifying post-operative complications based on the type of treatment needed to correct the complication. Grade I requires the least treatment; grade V is death. The number and proportion of participants with PC will be presented. No minimal important difference (MID) level for the CD system is recommended, and in the present study, a difference of 1 grade is considered important and was used in the power calculations for sample size.

Time-point: 30 days post-surgery (*t*_4_)

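### The exercise itself is the only reason given for leaving care providers unblinded, but it does not cover the surgical, anaesthetic and ward staff whose treatment choices set the Clavien-Dindo grade

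*Protocol article*

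**What the plan says.** The section on who will be blinded {17a} makes three statements.

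- On assessors: "Outcome assessors are blinded".
- On everyone else: "Due to the nature of the intervention (exercise), neither care providers nor participants could be blinded".
- On protecting the blind: "Participants are instructed not to reveal their assignment to assessors at the follow-ups". The time points listed are t−1, t2 and t3.

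Delivery is described under Study setting {9}: "Physiotherapists (PT) from the Stockholm County home-rehabilitation units will deliver the intervention in the participants’ homes". Its timing is under Intervention description {11a}: "The intervention group will receive moderate- to high-intensity physical exercise for 14–17 days before surgery".

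Under Primary outcomes, the second primary outcome is the Clavien-Dindo grade at 30 days (t4), described as a system for "quantifying post-operative complications based on the type of treatment needed to correct the complication". Under Secondary outcomes, length of stay ends on the day the surgeon considers the patient ready for discharge.

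Four other places bear on who learns the allocation.

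- Section {11b} has the responsible surgeon contacted when an adverse event occurs, to decide whether the programme continues.
- Section {22} sends suspected adverse events to the responsible physician and the site lead investigator.
- The Lead investigators section makes that person a senior surgeon, and section {21a} gives lead investigators unblinded access to participant data.
- Section {17b} declares an unblinding procedure not applicable.

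**The concern.** One reason is given for leaving a whole class of people unblinded, and it applies to only part of that class. Exercise cannot be hidden from the person doing it or the person supervising it. It can in large part be hidden from a hospital team that meets the patient after the programme has ended.

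The distinction matters because of how this outcome is built. The Clavien-Dindo grade records what was done about a complication, so the treating clinician's decision is an input to the endpoint. If that clinician knows the arm and manages an exercised patient even slightly more conservatively, a lower grade is entered in the record. A blinded grader will then score it faithfully. Length of stay is exposed in the same way through the surgeon's discharge decision.

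**Working it through.** **Sample size, for reference.** The concern disputes no figure, but the Clavien-Dindo inputs are reused below and they reproduce. With a difference of 1 grade, SD 1.32, two-sided 5% and power 0.80, the t-test solution is 28.34 per arm. That rounds to 29, or 58 in total, and 58/0.864 = 67.1, against the stated 67.

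**Does the stated reason reach each group?**

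| Group | Delivers or performs the exercise? | Influences the Clavien-Dindo grade? | Kept unaware by the plan? |
|---|---|---|---|
| Participants | Yes | – | No; reason applies |
| Home-rehabilitation physiotherapists | Yes ({9}) | No role described | No; reason applies |
| Outcome assessors | No | Record it | Yes ({17a}) |
| Surgical, anaesthetic and ward staff | No role described | Yes, through the treatment chosen | No; reason does not apply |

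The non-disclosure instruction covers assessors only. It does not name ward or surgical staff, and it stops at t3, before the 30-day complication window closes at t4. One of its three time points, t−1, is enrolment in the Table 1 legend and so precedes randomisation.

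**How much masking is feasible under the protocol's own arrangements?**

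- In favour: randomisation follows baseline and is done in REDCap by four members of the trial team ({16c}). The sequence is concealed from all but two people ({16b}). The physiotherapists belong to home-rehabilitation units and work in the participants' homes. The multidisciplinary conference precedes randomisation, so it can reveal likely participation but not the arm.
- Against: adverse-event contact tells the responsible surgeon the arm ({11b}, {22}). Each site's lead surgeon has unblinded access ({21a}). Participants know their arm.

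Masking is therefore feasible for much of the staff, but not all.

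**Size, as an illustration only.** The following inputs are assumptions, not taken from the documents.

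- Control grades 0/I/II/III/IV/V are 55/12/18/10/3/2%.
- There are 80 per arm and no true effect.
- A fraction d of exercise-arm grade I–III complications comes out one grade lower.
- The Mann-Whitney test stands in for ordinal logistic regression.

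The assumed distribution has mean 0.12 + 0.36 + 0.30 + 0.12 + 0.10 = 1.00 and mean square 0.12 + 0.72 + 0.90 + 0.48 + 0.50 = 2.72. The SD is √(2.72 − 1.00) = 1.31, close to the protocol's 1.32. Grades I–III make up 40%, so the mean shift is 0.40 × d.

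An approximate check uses SE = 1.32 × √(2/(80 × 0.864)) = 0.2245 and the false-positive probability Φ(shift/SE − 1.96).

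| d | Mean shift (grades) | False positive favouring exercise, simulated | Approximation |
|---|---|---|---|
| 0 | 0 | 2.5% | 2.5% |
| 10% | 0.04 | 3.9% | 3.7% |
| 20% | 0.08 | 5.8% | 5.4% |
| 30% | 0.12 | 8.5% | 7.7% |
| 40% | 0.16 | 13.1% | 10.6% |

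The simulated column is from 6,000 replicates per row. A repeat with 10,000 gave 2.4, 3.9, 5.7, 8.9 and 12.2%. The planned analysis is two-sided. Total two-sided error in the same set-up was about 4.6% at d = 0, 5.2% at 10% and 6.8% at 20%.

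**The case against.** **Care providers may mean only the physiotherapists.** The reason given fits them, and section {30} uses the same term for those who would deliver the regimen. On that reading the sentence is correct as it stands. This is fair as to wording, but it does not close the gap: the section would then say nothing about peri-operative staff, and on either reading nothing keeps them unaware.

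**Masking cannot be complete.** A reader might infer that all hospital staff can be kept unaware and the bias removed at almost no cost. The documents do not support that. Surgeons learn the arm through adverse events, lead surgeons have unblinded access, and a request for silence over a whole admission is harder to keep than one covering a few test sessions. No adverse-event rate is given, so disclosures cannot be assumed to be few. This objection stands, and the claim is limited to reducing the exposure.

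**The size is assumed.** It is. No passage supports the direction, the one-sidedness or the rate of downgrading. At 20% the mean moves by 0.08 grade against a planned difference of 1 grade, and two-sided error rises only to about 6.8%. This also stands.

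**Unmasked clinical care is ordinary in exercise trials.** That may be so, but here treatment choice defines a primary outcome, and the protocol already has an instruction that could be extended.

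**Conclusion.** The concern holds in limited form. The only reason given for not blinding care providers does not extend to surgical, anaesthetic and ward staff, and assessor blinding alone does not protect the second primary outcome from their knowledge of the arm. Length of stay shares the exposure. Masking these staff would reduce it, not eliminate it.

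The conclusion rests on the protocol's own account of who delivers the exercise, when, and what determines the grade. It does not rest on the simulation. The range of about 4% to 13% against a nominal 2.5% shows what modest downgrading could do under assumed grades and rates; it does not estimate what will happen in this trial. Nor do the documents show that any clinician would treat the arms differently. The point is worth acting on because the change is small and a primary outcome is involved.

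**What to change.** Revise section {17a} and bring the related sections into line.

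1. Separate two groups: participants and exercise physiotherapists, who are unblinded for the stated reason; and surgical, anaesthetic and ward staff, who are not routinely told the allocation.
2. Extend the instruction not to reveal assignment to ward and surgical staff and through t4. Check the t−1 entry against the Table 1 legend at the same time.
3. State the exceptions that already exist: adverse-event contact with the responsible surgeon ({11b}, {22}) and lead-investigator access for safety (Lead investigators section, {21a}). Say what happens when a lead investigator also treats participants.
4. Reconcile section {17b}, which calls unblinding not applicable, with those exceptions.
5. Log each disclosure to treating staff, with its date and the role of the person told.

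The cost is wording, a revised participant instruction and a disclosure log, with no extra participants, visits or analyses. Masking will be incomplete, and safety communication to the treating surgeon must stay exactly as it is. Trial status gives recruitment from March 2021 to about June 2023, so the change can help only participants not yet operated on. For the others, the trial report should say that no procedure kept treating staff unaware of the allocation.

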**Table 1 Tab1:**
[figure not shown]
Participant timeline

*t_-1 enrolment_, t_0_ = baseline assessment and point of randomization, t_1_= admission, t_2_ = two to three days post-surgery, t_3_ = ready to discharge, t_4_ = 30 days post-surgery, t_5_ = 6-month post-surgery, t_6_ = 1-year post-surgery, t_7_ = 2 years post-surgery t_8_ = 3 years post-surgery/close-out. X_a_ = PRP original version, X_b_= PRP hospital version excluding questions 11 and 12.

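### The list of visits at which participants must not disclose their allocation names enrolment (t−1) and omits admission (t1), where the primary 6MWT is repeated

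*Protocol article*

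**What the plan says.** Section {17a} states that outcome assessors are blinded and that participants and care providers cannot be. It then gives the supporting measure: "Participants are instructed not to reveal their assignment to assessors at the follow-ups", with the follow-ups listed in brackets as t−1, t2 and t3. The section on the data monitoring committee {21a} repeats that assessors are blinded.

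The legend to Table 1 gives t−1 as enrolment and defines the next visits as follows: "t_0_ = baseline assessment and point of randomization, t_1_= admission, t_2_ = two to three days post-surgery, t_3_ = ready to discharge". The implementation section {16c} agrees on the order of events: "After the first baseline visit (*t*_0_), participants are randomised and allocated using the randomisation function".

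Under Primary outcomes, the first primary outcome is the "change in walking distance during a 6-min walk test (6MWT) [34] during the pre-operative period". Its schedule reads: "Time points: Baseline (*t*_0_), at hospital admission (or the day before (*t*_1_), and at discharge from hospital (*t*_3". Under Secondary outcomes, the 30-second chair stand test and maximal inspiratory pressure (MIP) have the same three time points.

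**The concern.** The list contains a visit at which the instruction can have no effect and leaves out one at which it matters. Before randomisation nobody knows the allocation, and enrolment is not a follow-up.

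Admission is different. Participants know their group, and those in the intervention arm arrive straight from 14–17 days of home exercise with at least six physiotherapist visits. The 6MWT is scored as the greatest distance the participant can cover, so the result depends on effort and can respond to encouragement. An assessor who learns the allocation might, without intending to, encourage one group more than the other. If the intervention group received more encouragement, the error would favour the intervention, and no later analysis could remove it.

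Assessor blinding is the only blinding in this trial, and the participant is an obvious route by which it could be lost. The non-disclosure instruction is the only measure the article describes against that route.

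**Working it through.** No arithmetic is needed. The check compares the visit labels across sections.

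1. **Visits the instruction covers** ({17a}): t−1, t2, t3.
2. **Meaning of the labels** (Table 1): t−1 enrolment; t0 baseline and randomisation; t1 admission; t2 two to three days after surgery; t3 ready for discharge.
3. **When an allocation first exists** (Table 1 and {16c}): at or after t0. It follows that t−1 cannot be a visit at which an assignment is disclosed.
4. **Performance-test visits** (Primary and Secondary outcomes): 6MWT, chair stand and MIP are each measured at t0, t1 and t3. Removing t0, which precedes randomisation, leaves t1 and t3.
5. **Comparison**: of these two post-randomisation performance-test visits, t3 is on the list and t1 is not. The t2 visit, which is listed, carries the recovery questionnaire and the delirium assessment.
6. **What depends on t1**: the first primary outcome is the change over the pre-operative period. Because t3 falls after surgery, that change is t1 minus t0, and t1 is its only post-randomisation measurement. Listing t3 does not protect it.
7. **Whether the labels are interchangeable elsewhere**: the sections on adherence {11c} and recruitment {15} offer taxi transport to t−1 and t1 as two separate pre-operative visits. There t−1 seems to be used loosely for the hospital baseline visit. That visit is still before randomisation, so step 3 is unaffected.

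The post-randomisation visits up to discharge are t1, t2 and t3. The printed list differs from this set by one label.

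**The case against.** The strongest reply is that this is a stray minus sign. The sentence speaks of follow-ups, enrolment cannot be one, and the only coherent reading is t1, t2, t3. On that reading the error lies in the text and says nothing about conduct. This is very likely right, and the proposed correction assumes it. The point still stands because the error sits in an operational rule about blinding, and because the article elsewhere treats t−1 and t1 as different visits, so a reader cannot simply exchange one for the other.

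A second reply is that assessors are declared blinded without limitation to any visit. That also stands, and it limits the point. A reader might infer that assessors were unblinded at admission, or that t1 alone lacks protection. The documents support neither: the general statement covers t1, and only the supporting instruction fails to name it.

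A reader might also want the 30-day complication grading (t4) added to the list. The instruction concerns what participants say to assessors, whereas post-operative complications are taken from medical records. How that record review is masked is detail that an article may leave to the full protocol.

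Finally, an article condenses its source. That excuses omitted detail, but here a list is given and one entry is wrong.

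**Conclusion.** The inconsistency is certain on the article's own definitions: the list includes a pre-randomisation visit and omits t1. It touches one of the two primary outcomes and two secondary performance measures, all at the same visit.

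The consequence is conditional. Bias would require that the list was applied as printed, that participants disclosed their group at admission, and that assessors responded to the knowledge. The article does not show that any of these happened, and it contains no figure from which the size of a bias could be derived, so none is given. Whether the written site instructions carry the same error cannot be judged, because they are not shown.

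The correction is worth making because it is specific, costs almost nothing, and protects the measurement on which the first primary outcome rests.

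**What to change.** - In section {17a}, change the list of visits to t1, t2 and t3, so that it agrees with Table 1 and the outcome schedule.
- Check that the participant and assessor instructions, and the written checklists mentioned under training of assessors {18a}, name t1.
- For admission visits already held, state what participants were actually told about disclosure.
- Optionally, add a yes/no field in which the assessor records, after testing, whether the allocation became known. This is good practice and is not needed to correct the error.

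The cost is one corrected label, a check of existing site documents and a short statement on past conduct. Sample size, visit schedule and analysis do not change.
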